## Study variables

### Exposure variables

The exposure of interest is the undertaking of lipid testing. Once a patient has their lipids recorded, this signifies that a clinician has made a decision about the significance of the lipid levels and will act on this. Individual patients may have multiple lipid results recorded over the study period. Assuming the exclusion criteria are not met, each lipid result will be considered as a new exposure so long as it is not within 60 days of the last recorded lipid level. The number of previous lipid results will be included in predictive modelling.

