**Methods and analysis:**

The Health Improvement Network (THIN) is a database of coded primary care electronic patient records from over 500 UK general practices. From this resource, a historical cohort will be created of patients without a diagnosis of CVD, not currently receiving a prescription for statins and who had a lipid profile measured. A post hoc QRISK2 score will be calculated for these patients and they will be followed up for 60 days to establish whether they were subsequently prescribed a statin. Primary analysis will consist of predictive modelling using multivariate logistic regression with potential predictors including cholesterol level, calculated QRISK2 score, sociodemographic characteristic and comorbidities. Descriptive statistics will be used to identify trends in prescribing and further secondary analysis will explore what other factors may have influenced the prescribing of statins and the degree of interprescriber variability.

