### Population

Patients will be eligible for inclusion if they are aged between 40 and 84 years inclusive (the age range recommended by the National Institute for Health and Care Excellence (NICE) for risk assessment^5^) with no previous diagnosis of CVD and at least one lipid result coded in the study period. The date of the first coded lipid result in the study period will be considered the index date. Patients must not have been prescribed a statin prior to the index date.

In order to maintain a stable cohort of practices, only THIN practices in which there are data available for the whole study period will be included. The study period will run from the beginning of 2012 to the end of 2016. Patients will be eligible for inclusion from the earliest of the following dates: study start date, acceptable mortality reporting date (which ensures that patient deaths and deregistrations are being recorded consistently^45^), Vision date plus 1 year, registration date plus 1 year (to ensure time for baseline data to be recorded), and age 40; until the earliest of the following dates: age 85, study end date, CVD diagnosis, other excluding diagnosis (as below), statin initiation or recording of a contraindication for the prescribing of statins. Patients will also be excluded if they left the database within 60 days of the index date.

Patients will be excluded if they had pre-existing CVD, were pregnant, had a contraindication to statin therapy (including allergies and drug interactions), were already being prescribed a statin (or other lipid-lowering therapy) or had ever been prescribed a statin in the past. Patients will be considered to have pre-existing CVD if they had a diagnosis of myocardial infarction, angina, peripheral vascular disease or stroke/transient ischaemic attack. Patients with type 1 diabetes mellitus, a diagnosis of chronic kidney disease stages 3–5 and patients diagnosed with or who were at risk of familial hypercholesterolaemia will also be excluded as statin use in these patients should not be based on CVD risk assessment. Patients at risk of familial hypercholesterolaemia will be defined as those with a total cholesterol of ≥9.0 mmol/L as this is the threshold for seeking specialist assessment defined in the NICE guidance.^5^

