### Outcome variables

The outcome will be the prescription of a statin within 60 days of a set of lipid results.

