### Predictor variables

Sociodemographic details will be obtained for each patient: age, sex, ethnicity, Townsend quintile and rurality indicator (see online supplementary appendix III). General practice and clinician ID will also be recorded.

10.1136/bmjopen-2016-013120.supp3supplementary appendix III

Patient variables will include the cardiovascular risk factors required to calculate QRISK2; age, sex, ethnicity, postcode, smoking status, diabetes status, family history of CVD, CKD (stage 4 or 5), atrial fibrillation, hypertension treatment, rheumatoid arthritis, lipids, blood pressure and body mass index (BMI). Other clinical data that may affect the decision to prescribe statins will also be collected comprising of; liver transaminase levels, systemic inflammatory conditions, severe mental health conditions and HIV.

Data on medication prescriptions will be extracted. Patients who received a prescription for antihypertensive medication up to 180 days prior to the index date will be considered to have been on treatment for hypertension. Prescriptions of antipsychotics, corticosteroids and immunosuppressant medication will be recorded as these may change the threshold for prescribing lipid-lowering medication.

All included patients will have a QRISK2 score calculated post hoc from the available data. In addition, any coded QRISK2 score prior to and including the follow-up period will be extracted.

The date when predictor variable data are collected will vary depending on whether or not the patient has a QRISK2 score coded during the follow-up period. For patients with a coded QRISK2 score on the index date or in the follow-up period, the date of QRISK2 recording will be used as the date for collecting data on predictor variables and the most recent data (including the date of QRISK2 coding) will be recorded. If more than one QRISK2 score is coded in the follow-up period, the latest date will be used for data collection to account for any variables that were updated during the follow-up period. For patients who do not have a coded QRISK2 score, the included data will be the most recent recorded before and including the end of the 60-day follow-up period.

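### A statin started after a repeat lipid test, but more than 60 days after the first test, falls in no outcome window and is coded as no statin

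*Protocol article*

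**What the plan says.** Under Exposure variables, a further lipid result in the same patient counts as "a new exposure so long as it is not within 60 days of the last recorded lipid level". The same section gives the reason for treating a recorded result as the exposure: "this signifies that a clinician has made a decision about the significance of the lipid levels and will act on this".

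Under Outcome variables, "The outcome will be the prescription of a statin within 60 days of a set of lipid results". The text does not say that the set must be the one that opened the exposure. The abstract describes a fixed follow-up: "they will be followed up for 60 days to establish whether they were subsequently prescribed a statin".

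Under Population, "The date of the first coded lipid result in the study period will be considered the index date". Among the events that end a patient's eligibility is "statin initiation or recording of a contraindication for the prescribing of statins".

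Under Predictor variables, for patients with no coded QRISK2 score, "the included data will be the most recent recorded before and including the end of the 60-day follow-up period". Where a score is coded on the index date or during follow-up, predictors are taken as at the date of that score.

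**The concern.** The exposure rule assumes that a recorded result marks a decision. A prompt repeat test is the obvious case in which the decision may have been put off until the second result. Under the stated rules that second result has no outcome window of its own, so a statin prescribed soon after it can belong to no exposure. The patient then contributes one row, coded as a non-initiator.

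The study's aim is to compare the influence of lipid levels with that of predicted risk on initiation. If the lost initiations are spread unevenly over lipid bands, the error bears on the main comparison. The planned yearly means for patients initiated and not initiated would also place these patients in the wrong group.

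**Working it through.** **1. The rules applied to example patients**

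| Lipid tests (day) | Statin (day) | Result under the stated rules |
|---|---|---|
| 0, 20 | 50 | Event: within 60 days of the day-0 test |
| 0, 45 | 70 | Day 0 closes at day 60 with no statin; day 45 is not an exposure; eligibility ends on day 70. No event, although 70 − 45 = 25 days after a result |
| 0, 50, 100 | 105 | Day 50 is 50 days after the last recorded level, and so is day 100 (100 − 50 = 50). Neither is an exposure. No event, although 105 − 100 = 5 days after a result |

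The third row takes the last recorded level literally. If it means the last counted exposure, day 100 qualifies (100 − 0 = 100 days) and the statin is an event. The second row is the same on both readings.

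**2. Predictor against outcome clock.** In the second row, with no coded QRISK2 score, the day-45 lipid value is the latest before day 60 and can be the predictor. The outcome clock still runs from day 0, leaving 60 − 45 = 15 days after that value. If a score was coded on day 0, the day-45 value is not used.

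**3. Share of post-repeat starts that is lost.** The plan gives no figure for repeat testing, so there is none to reproduce, and every input here is an assumption. Let the repeat day r be uniform from day s to day 60. Let the delay d from repeat to statin be exponential with mean m, restricted to d ≤ 60. With L = 60 − s,

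P(r + d > 60 | d ≤ 60) = [(m/L)(1 − e^(−L/m)) − e^(−60/m)] / (1 − e^(−60/m)).

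- Low end, s = 7, m = 10: [(10/53)(1 − e^(−5.3)) − e^(−6)] / (1 − e^(−6)) = (0.1877 − 0.0025)/0.9975 = 0.186.
- High end, s = 30, m = 30: [(1 − e^(−1)) − e^(−2)] / (1 − e^(−2)) = (0.6321 − 0.1353)/0.8647 = 0.575.

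For s of 7, 14 or 30 and m of 10 to 30 days, the share therefore runs from about 19% to 57%.

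**4. Effect on the lipid association.** Assume true initiation of 8% with high and 2% with low total cholesterol. The true odds ratio is (0.08/0.92)/(0.02/0.98) = 4.26. Observed initiation in a group is p × (1 − share following a repeat × share of those lost).

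| Initiations following a repeat, high / low | Lost | Observed high | Observed low | Odds ratio |
|---|---|---|---|---|
| 20% / 5% | 19% | 7.696% | 1.981% | 4.13 |
| 20% / 5% | 30% | 7.52% | 1.97% | 4.05 |
| 20% / 5% | 50% | 7.20% | 1.95% | 3.90 |
| 40% / 5% | 30% | 7.04% | 1.97% | 3.77 |
| 40% / 5% | 50% | 6.40% | 1.95% | 3.44 |
| 20% / 20% | 50% | 7.20% | 1.80% | 4.23 |

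For example, row 5 is (0.064/0.936)/(0.0195/0.9805) = 3.44. Taking the top loss of 57% with 40% / 5% gives (0.06176/0.93824)/(0.01943/0.98057) = 3.32.

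Higher assumed initiation gives the same direction. With 30% against 10% (odds ratio 3.86), repeats before 30% / 5% of initiations and 10–70% of those lost, the odds ratio is 3.71 to 2.91.

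**The case against.** A fixed window from the first test is a legitimate, uniform definition, and any fixed window loses later starts, including those after a single test. That stands as a reason to keep the first-result analysis. It does not settle the matter, because the outcome section refers only to a set of lipid results, and the day-70 statin satisfies those words through the day-45 test. On that looser reading the patient is an event; on the exposure and follow-up rules the patient is not. Two analysts could code the same patient differently.

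The chaining problem depends on taking the last recorded level literally; the authors may have meant the last counted exposure. That also stands, and it is a reason to say so in the text.

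Three stronger conclusions are tempting and should not be drawn:

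- **That every statin started after a confirmatory test is lost.** Only those later than day 60 of the first test are. Under the assumptions above, 43–81% of post-repeat starts are still counted.
- **That the losses are concentrated in patients with raised lipids.** This is plausible, but the documents say nothing on how often tests are repeated or in whom.
- **That the primary definition should become a testing episode of variable length.** Repeat-tested patients would then have longer to be counted as initiators. If repeats do cluster at high lipid levels, that could inflate the lipid effect.

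**Conclusion.** The point holds as a narrow defect in the stated rules. Some initiations that follow closely on a lipid result belong to no window and are coded as no statin, and the exposure, outcome and predictor sections do not agree on which result sets the clock.

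The direction is towards the null for the lipid association only if repeat testing before treatment is commoner with raised lipids. Under the assumed inputs, an odds ratio of 4.26 is then seen as about 4.13 (a change of 3%) to 3.44 (19%), or 3.32 at the highest loss considered. With repeats unrelated to lipid level it is 4.23, a negligible change. These are unadjusted two-group illustrations and not estimates of the planned model's coefficients. A strong lipid association would survive in all of these cases, but the study compares lipids with risk, so the relative size matters. The correction is worth making before extraction.

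**What to change.** 1. Reconcile the exposure, outcome and predictor sections by naming the result that anchors the 60-day window and the result whose value enters the model.
2. Measure the 60-day gap from the last counted exposure, so that chained tests are not lost. This recovers the day-0/50/100 case but not the day-0/45/70 case, which is why the next two steps are needed.
3. Report the number of statin initiations that fall within 60 days of a lipid result but in no window, by total cholesterol band and QRISK2 band. This replaces the assumptions above with data.
4. Add a sensitivity analysis that treats results no more than 60 days apart as one episode, with the outcome window and the lipid value anchored to the last result before the statin, or to the last of the episode if there is none.

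The cost is a clearer definition, one table and one further model run, all on data already extracted. In the episode analysis, repeat-tested patients have a longer window, and the choice of lipid value depends partly on whether a statin was started. It should therefore sit beside the first-result analysis and not replace it.

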### Outcome variables

The outcome will be the prescription of a statin within 60 days of a set of lipid results.

### Predictor variables

Sociodemographic details will be obtained for each patient: age, sex, ethnicity, Townsend quintile and rurality indicator (see online supplementary appendix III). General practice and clinician ID will also be recorded.

10.1136/bmjopen-2016-013120.supp3supplementary appendix III

Patient variables will include the cardiovascular risk factors required to calculate QRISK2; age, sex, ethnicity, postcode, smoking status, diabetes status, family history of CVD, CKD (stage 4 or 5), atrial fibrillation, hypertension treatment, rheumatoid arthritis, lipids, blood pressure and body mass index (BMI). Other clinical data that may affect the decision to prescribe statins will also be collected comprising of; liver transaminase levels, systemic inflammatory conditions, severe mental health conditions and HIV.

Data on medication prescriptions will be extracted. Patients who received a prescription for antihypertensive medication up to 180 days prior to the index date will be considered to have been on treatment for hypertension. Prescriptions of antipsychotics, corticosteroids and immunosuppressant medication will be recorded as these may change the threshold for prescribing lipid-lowering medication.

All included patients will have a QRISK2 score calculated post hoc from the available data. In addition, any coded QRISK2 score prior to and including the follow-up period will be extracted.

The date when predictor variable data are collected will vary depending on whether or not the patient has a QRISK2 score coded during the follow-up period. For patients with a coded QRISK2 score on the index date or in the follow-up period, the date of QRISK2 recording will be used as the date for collecting data on predictor variables and the most recent data (including the date of QRISK2 coding) will be recorded. If more than one QRISK2 score is coded in the follow-up period, the latest date will be used for data collection to account for any variables that were updated during the follow-up period. For patients who do not have a coded QRISK2 score, the included data will be the most recent recorded before and including the end of the 60-day follow-up period.

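### Treated hypertension is fixed at the index date but blood pressure is read up to day 60 or the QRISK2 coding date, so one calculated score can pair an on-treatment pressure with untreated status

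*Protocol article*

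**What the plan says.** The Predictor variables section of the protocol article lists treatment and pressure together among the inputs needed for the calculated QRISK2: "hypertension treatment, rheumatoid arthritis, lipids, blood pressure and body mass index (BMI". It then gives two timing rules.

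- **Treatment.** The rule for those prescribed such drugs reads, in part: "antihypertensive medication up to 180 days prior to the index date will be considered to have been on treatment for hypertension". Nothing is said about prescriptions after the index date.
- **Predictors in general.** If a QRISK2 score is coded on the index date or in follow-up, "the date of QRISK2 recording will be used as the date for collecting data on predictor variables". If several are coded, "the latest date will be used for data collection to account for any variables that were updated during the follow-up period". If none is coded, "the included data will be the most recent recorded before and including the end of the 60-day follow-up period".

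Blood pressure falls under the general rule. No sentence extends the prescription window to the collection date, and none excludes a pressure taken after treatment has begun.

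The Population section defines the anchor: "The date of the first coded lipid result in the study period will be considered the index date". The Exposure variables section then treats each later lipid result as a new exposure, provided it is not within 60 days of the previous one.

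**The concern.** Two inputs of one risk score are read on different dates. A patient who starts an antihypertensive between those dates can be entered with the pressure that treatment produced but without the treatment. Both halves of that pairing tend to lower the score.

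The late collection date is there "to account for any variables that were updated during the follow-up period". Treatment status is such a variable, yet its own sentence stops at the index date.

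Calculated QRISK2 and systolic pressure are both predictors in the primary model (Table 1), and the study's aim is to compare the roles of lipid level and predicted risk in statin initiation. The article also plans to test the accuracy of the post hoc score against coded scores. A clinician's score that already reflects new treatment could differ from the post hoc score because of the date rule alone.

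**Working it through.** The article gives no figure on this point to reproduce. The check is therefore a comparison of the windows, followed by an illustration with assumed weights.

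**1. The windows, with day 0 as the index date**

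| Input | Window in the article |
|---|---|
| Hypertension treatment | day −180 to day 0 |
| Blood pressure, QRISK2 coded on day c (0 to 60) | latest value up to day c |
| Blood pressure, no coded score | latest value up to day 60 |

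For a first exposure the cut-offs differ by 0 to 60 days.

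**2. Which patients are affected**

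- First antihypertensive in the 180 days before the index date: flagged as treated, no mismatch.
- First antihypertensive after the index date, no new pressure by the collection date: pre-treatment pressure with untreated status, a coherent pre-treatment score.
- First antihypertensive after the index date, new pressure after that start and by the collection date: on-treatment pressure with untreated status. This is the defect.

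A made-up record shows the third case. There is no coded score, systolic pressure is 168 on day 0, the first antihypertensive is on day 7, and pressure is 138 on day 45. The literal rule enters 138 (Table 1 category <140) and untreated. The patient was 168 untreated and later 138 treated, never 138 untreated.

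**3. Repeat exposures**

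Read literally, the index date is the first lipid result of a study period running from 2012 to 2016. For a later exposure the treatment flag would still refer to that first result while the pressure is current. The gap can then exceed 60 days, possibly by years.

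**4. Size for one affected patient**

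All weights here are assumptions, because the article gives none:

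- CVD hazard ratio per 10 mm Hg systolic: s = 1.05 to 1.10
- recorded fall on treatment: d = 20 to 30 mm Hg
- hazard ratio for treated hypertension: h = 1.2 to 1.8
- score on consistent index-date inputs: p = 12%

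Literal rule: 1 − (1 − p)^m, with m = s^(−d/10).
Both inputs taken late: 1 − (1 − p)^(m·h).

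| s, d | m | Literal rule | Both late, h = 1.2 | Both late, h = 1.8 |
|---|---|---|---|---|
| 1.05, 20 | 0.907 | 10.9% | 13.0% | 18.8% |
| 1.10, 30 | 0.751 | 9.2% | 10.9% | 15.9% |

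The literal rule gives 9.2–10.9%, against 12.0% with both inputs at the index date and 10.9–18.8% with both late. A smaller assumed fall of 10 mm Hg at s = 1.05 gives 1 − 0.88^(1/1.05) = 11.5%.

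Starting instead from a consistent late score of 12% and removing only the flag gives 1 − 0.88^(1/h) = 10.1%, 8.2% and 6.9% for h = 1.2, 1.5 and 1.8.

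The QRISK2 bands are cut at 10, 15 and 20%, so an affected patient can change band. Against index-date inputs the shift is modest, and a 12% patient leaves the band only near the strong end of the assumptions. Against late inputs it is larger.

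**The case against.** **The section can be read consistently.** The closing paragraph speaks of predictor variables as a whole, so the 180-day sentence might only set a look-back length. That reading is possible, but the sentence names the index date as its anchor. The section then holds two timing rules for one variable, and an analyst cannot tell which to program. It needs correcting on either reading.

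**An index-date flag is defensible.** An antihypertensive begun after the lipid result may be prescribed together with the statin, and counting it would bring a concurrent decision into a model of initiation. This stands. It argues for moving the pressure back rather than the flag forward, and it shapes the fix below.

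**The mismatch is narrow.** It needs a post-index start, a new reading, and a reading dated by the collection date. This also stands. A reader might infer that every newly treated patient is scored too low, but the windows do not support that.

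**The plan partly covers it.** The comparison with coded scores could reveal the mismatch, but only in patients who have a coded score, and it would not correct the others. The article's general admission that approximations will be needed concerns incomplete recording, not a date rule.

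**Conclusion.** The inconsistency is in the text and should be corrected. Followed literally, the rule can produce a calculated QRISK2 from a combination of inputs that existed on no date. The downward direction rests on a positive weight for treated hypertension, which its listing as a risk factor implies, or on a recorded fall in pressure. With the assumed weights, a patient at 12% on index-date inputs is scored about 9–11%.

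The effect on the primary model cannot be sized. The article does not say how many patients start an antihypertensive in the window, how often pressure is re-recorded, or what the weights are.

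Two stronger conclusions might be inferred, and neither is supported:

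- That the rule weakens the QRISK2 association relative to cholesterol. This requires affected patients to be more likely to start a statin, which the article does not show.
- That the Hypertension coefficient in Table 1 is distorted. The article does not say that this variable is the 180-day prescription flag.

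**What to change.** Use one reference date per exposure for every QRISK2 input. End the 180-day antihypertensive look-back on the same date up to which blood pressure is taken, and tie the index date to each exposure's own lipid result.

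Preferably that date is the lipid-result date. It is defined in the same way for initiators and non-initiators, and it keeps out treatment started with or after the statin. In any case it should be no later than the statin prescription. Simply moving the flag forward to day 60 would remove the mismatch but would let such treatment count as a predictor.

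The cost is one sentence in the variable definition and one date in the extraction code, with no new data. The treatment flag must then be derived separately for each exposure. With the lipid-result date, values updated during follow-up no longer enter the model. If they are wanted for the comparison with coded scores, a second calculation with all inputs, including treatment, taken at the coding date would serve.

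### Predictor values may be dated after the statin prescription they are meant to predict, because the predictor and outcome windows overlap with no cut at initiation

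*Protocol article*

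**What the plan says.** Under Outcome variables: "The outcome will be the prescription of a statin within 60 days of a set of lipid results".

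Under Predictor variables, the dating rule depends on whether a QRISK2 score was coded:
- No coded score: "the included data will be the most recent recorded before and including the end of the 60-day follow-up period".
- Score coded on the index date or in follow-up: "the date of QRISK2 recording will be used as the date for collecting data on predictor variables".
- Several scores coded in follow-up: "the latest date will be used for data collection to account for any variables that were updated during the follow-up period".

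The same section lists lipids, blood pressure, BMI and smoking as QRISK2 inputs, and transaminases as further clinical data, with no separate date for any of them. Coded scores are extracted up to the end of follow-up. One predictor has its own pre-index rule, treatment for hypertension: "Patients who received a prescription for antihypertensive medication up to 180 days prior to the index date".

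On repeat tests, Exposure variables says that "each lipid result will be considered as a new exposure so long as it is not within 60 days of the last recorded lipid level". Population names, among the events that end a patient's eligibility, "statin initiation or recording of a contraindication for the prescribing of statins". The predictor rule does not refer to that list.

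**The concern.** The first objective is to see how lipid levels and CVD risk independently predict subsequent prescribing. A value recorded after the prescription cannot have informed it. A patient started on day 5 may have a safety transaminase, a new blood pressure or BMI entry, a QRISK2 code or a repeat lipid test by day 60, and the stated rule would use each of these as a predictor.

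Three consequences follow.
- **Lipids and calculated QRISK2.** An on-statin cholesterol can occur only in initiators, so any such value lowers cholesterol selectively in patients with the outcome. The yearly mean lipid levels and QRISK2 scores of initiators and non-initiators, planned under Analysis, are exposed in the same way.
- **Recording itself.** Missing data and extreme values keeps a 'missing' category because missingness may be associated with initiation. If starting a statin prompts a recording, 'missing' partly encodes the outcome. A QRISK2 coded after the prescription likewise counts as a coded score.
- **Unequal cut-offs.** Patients with a coded QRISK2 have predictors taken at the coding date, and those without at day 60. The third objective compares these two groups.

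Potential limitations does not mention the issue.

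**Working it through.** **Timing.** The outcome window is day 0 to day 60. The predictor window ends at day 60 (uncoded) or at the last coding date between day 0 and day 60 (coded). If the prescription is on day *d*, any value dated after *d* and up to that cut-off is admissible. The two windows close together only when the prescription falls on the cut-off itself.

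**The plan's own figure.** The minimum of 10 × 57 = 570 initiations reproduces. It is a precision rule and does not change with predictor dating.

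**Size for cholesterol.** The article gives no retest share, so all inputs here are assumptions: total cholesterol normal with mean 5.5 and SD 1.0 mmol/L; 7% initiation; true odds ratios of 1.8 (5.0–6.9) and 3.5 (≥7.0) against <5.0, using the Table 1 bands; a 25% fall on a statin; and a share *q* of initiators whose modelled value is the on-statin one.

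1. Population shares of the bands are 30.9%, 62.4% and 6.7%. With baseline odds of 0.0456, the initiation risks are 4.4%, 7.6% and 13.8%, about 7% overall.
2. Initiators therefore lie 19.2%, 67.7% and 13.1% in the three bands.
3. After a 25% fall, a value stays ≥7.0 only if it began at 9.33 or more, and drops below 5.0 if it began below 6.67. The same initiators now lie 80.9%, 19.1% and 0.0%.
4. Non-initiators do not move, so the observed odds ratio is the true one × (mixed band share ÷ mixed reference share) ÷ (true band share ÷ true reference share).

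For ≥7.0 at *q* = 20%:
- Mixed ≥7.0 share: 0.8 × 0.131 = 0.105.
- Mixed <5.0 share: 0.8 × 0.192 + 0.2 × 0.809 = 0.315.
- Odds ratio: 3.5 × (0.105/0.315) ÷ (0.131/0.192) = 1.71.

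| Share of initiators with on-statin value | OR ≥7.0 (true 3.5) | OR 5.0–6.9 (true 1.8) | OR ≥7.0 if the fall is 20% to 30% |
|---|---|---|---|
| 1% | 3.36 | 1.73 | 3.38 to 3.34 |
| 2% | 3.22 | 1.67 | 3.26 to 3.19 |
| 5% | 2.87 | 1.50 | 2.94 to 2.81 |
| 10% | 2.38 | 1.26 | 2.50 to 2.30 |
| 20% | 1.71 | 0.94 | 1.84 to 1.61 |

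A separate simulation (400,000 records, a second risk covariate, true odds ratios of 2.0 and 6.0, falls of 20–30%) shows the same pattern. The ≥7.0 odds ratio is 6.10 with the index value, 5.47–5.52 at 2%, 4.55–4.91 at 5% and 2.39–2.88 at 20%.

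**Size for a 'missing' category.** Assume half of patients already have a transaminase on record, and that a new one is recorded in the window for 30% of initiators and 5% of non-initiators. Missing shares are 0.5 × 0.70 = 0.35 and 0.5 × 0.95 = 0.475. The odds ratio is (0.35/0.65) ÷ (0.475/0.525) = 0.60 where the truth is 1. With 60% already on record it is (0.28/0.72) ÷ (0.38/0.62) = 0.63.

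**The case against.** Four points on the other side carry weight.

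- **The exposure result may be what is modelled.** Exposure variables and Outcome variables treat a particular lipid result as the exposure, and the day-60 rule sits under Predictor variables, where lipids appear as a QRISK2 input. A reader might infer that the plan certainly overwrites the cholesterol that prompted the decision. The text does not support that. It leaves open which lipid value is modelled, and a repeat within 60 days is one admissible reading. On the other reading, coded QRISK2, transaminases, 'missing' status and the unequal cut-offs remain affected.
- **Not every predictor can be altered.** Age, sex, ethnicity, deprivation and rurality cannot be changed by a statin, and hypertension treatment is fixed before the index date. Nothing in the article shows that a statin changes blood pressure, BMI or smoking. For these, the issue is that a post-prescription contact may generate or update the record.
- **Later values can be legitimate.** Data entered between the blood test and the prescription may be what the clinician used, and capturing updates is the stated purpose. This justifies values up to the prescription but none after it.
- **The size is not anchored.** Only retests after the prescription and inside the window count, and one taken within days of starting would not show the full fall. At 2% the ordering of the bands survives. The effect on calculated QRISK2 has not been computed; lipids are one of 14 listed inputs and the score is cut into four bands. The transaminase 'missing' coefficient answers no stated objective by itself.

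**Conclusion.** The concern holds. As written, the rule allows information recorded after the outcome to act as a predictor in the primary model, and nothing elsewhere in the article prevents it. Making initiation an end of eligibility does not do so, because the predictor rule runs to the end of follow-up or to the coding date regardless.

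Where an on-statin cholesterol is used, the lipid odds ratios move towards the null and, at high retest shares, past it for the middle band. A calculated QRISK2 that used the same value would also be lowered in initiators, by an amount not established here. Sample size does not help, because the error occurs only in patients with the outcome.

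The size is conditional. Under the assumptions shown, an odds ratio of 3.5 becomes about 3.2 if 2% of initiators are affected, 2.8–2.9 at 5% and 1.7 at 20%. A reader might conclude that the primary odds ratios will be roughly halved. The article gives no retest share, so this cannot be said: the bias could be small, but the protocol neither shows nor ensures it. The case for change rests on the dating rule, which decides whether the odds ratios can be read as prediction of a later decision.

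**What to change.** For the prediction models:
- Take total cholesterol, HDL and the lipids in the calculated QRISK2 from the result that defines each exposure. Say 'each exposure', because Population defines the index date as the first lipid result in the study period while Exposure variables admits later ones. Tying everything to the index date would give later exposures out-of-date predictors.
- Take all other predictors as the most recent value on or before the date of that exposure's lipid result, with the same rule for patients with and without a coded QRISK2.
- Count a coded QRISK2 only if it does not post-date the statin prescription. State a comparable limit for non-initiators, who would otherwise have longer to acquire a code.
- As a sensitivity analysis, admit later values dated before the prescription, again with a comparable cut-off for non-initiators.
- Keep the QRISK2 coding date only for the planned agreement check of post hoc against coded scores, which needs inputs from that date.

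The cost is a rewritten paragraph and a different date filter at extraction; the 570-event minimum is unchanged. The main model will have slightly more missing blood pressure, BMI and smoking data, and will lose some values recorded between the blood test and the prescription. The sensitivity analysis recovers those values.
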